### Statistical analysis

The analyses will be performed using the intention-to-treat principle. To assess whether intervention is related to a reduced risk of events we will use a chi-square analysis comparing the observed absolute risks across treatment groups. In addition, treatment efficacy will be assessed using a Cox regression model and expressed as a hazard ratio with corresponding 95 % confidence intervals. Since this is a randomized controlled trial, no adjustments will be made, although centers may be added. Associations will be considered significant at p < 0.05. All statistical tests will be 2 sided. For statistical analyses we will use SPSS (SPSS for Windows, Chicago, Ill, SPSS Inc.).

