**Design:**

The GROUND study is designed as a prospective, multi-center, randomized clinical trial. Patients with peripheral arterial disease, but without symptomatic cardiac disease will be asked to participate. All patients receive a proper risk factor management before randomization. Half of the recruited patients will enter the 'control group' and only undergo CT calcium scoring. The other half of the recruited patients (index group) will undergo the non invasive cardiac imaging algorithm followed by evidence-based treatment. First, patients are submitted to CT calcium scoring and CT angiography. Patients with a left main (or equivalent) coronary artery stenosis of > 50% on CT will be referred to a cardiologist without further imaging. All other patients in this group will undergo dobutamine stress magnetic resonance (DSMR) testing. Patients with a DSMR positive for ischemia will also be referred to a cardiologist. These patients are candidates for conventional coronary angiography and cardiac interventions (coronary artery bypass grafting (CABG) or percutaneous cardiac interventions (PCI)), if indicated. All participants of the trial will enter a 5 year follow up period for the occurrence of cardiovascular events. Sequential interim analysis will take place. Based on sample size calculations about 1200 patients are needed to detect a 24% reduction in primary outcome.

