### Sample size considerations

The sample size is determined by the estimated risk in the group of patients randomized to usual care (control group, A, figure 1) and the risk observed in the groups that undergo cardiac imaging followed by subsequent treatment by a cardiologist as outlined in the protocol (groups B to D). Based on earlier studies in the Netherlands the 5-year-risk in the control group is assumed 24%[42]. The 5 year risk of cardiovascular morbidity and mortality among the IC patients that undergo cardiac imaging and subsequent treatment is based on the sum of **I) **the risk observed in those with stenosis in the main left coronary artery (group B, figure 1) plus **II) **the risk observed in those with limited vessel disease but no ischemia during the dobutamine stress test (group D) plus **III) **the risk observed in those with limited coronary vessel disease but with ischemia during the dobutamine stress test (group C).

The prevalence of these subgroups B to D in the arm of cardiac imaging and subsequent treatment is estimated to be 8% for B; 70% for D and 22% for C. Using the literature we have estimated the risk of cardiovascular morbidity and mortality for these groups of patients belonging to category B to D.

The 5-year risk of cardiovascular morbidity and mortality in these subgroups is 66% for those with stenosis of the left main coronary artery[41] (group B), 32.8% for those with cardiac ischemia during the stress test (group C) and 16.4% for those without cardiac ischemia (group D).

The estimates for patients in categories C and D are based on the assumption that those with cardiac ischemia have a doubling of risk compared with those without cardiac ischemia and that the risk of all groups combined should add up to 24%.

The effects of interventions performed by the cardiologist on the risk observed in PAD patients who undergo cardiac imaging are based on published international data from the ACC and AHA guidelines. These effects are for the two appropriate subgroups: 70% reduction in 5-year event rate using reperfusion therapy (PCI/CABG) for group B and 40% reduction in 5-year event rate using reperfusion therapy (PCI/CABG) for group C. Patients without cardiac ischemia (group D) will receive no treatment.

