Based on these estimates, the 5-year risk of cardiovascular morbidity and mortality will be 17.4 % in the intervention group (the combined risk for groups B and C; 70% event reduction in the group with a risk of 66% applying to 8% of the population; 40% event reduction in the group of patients with a risk of 32.8% applying to 22% of patients), reflecting an estimated relative reduction in cardiovascular morbidity and mortality of 24%.

The total number of patients randomized to achieve this goal, with a two-sided alpha of 0.05 and 80% power will be 1222. For this calculation we used dedicated software ('Power', dr. [name], Erasmus Medical Center, Rotterdam, the Netherlands). A study of this size has a statistical power of 80% at a two-sided alpha level of 0.05. The reason for using interim analysis [43] is that on average fewer patients are needed in the study when the expected difference in the primary outcome variable is real or when no difference can be expected anymore, therefore increasing efficiency. Sequential analyses are performed on survival outcome variables according to the double triangular test as described by Whitehead [44] and implemented in the computer program PEST version 4 [45]. The sequential (interim) analyses will be performed every three months by an independent data safety monitoring board (DSMB).

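### The first-named efficacy test is a chi-square on crude risks with no time point and no rank against Cox; if the trial stops early or follow-up is incomplete, those risks are not the 5-year risks used for sizing

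*Protocol article*

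**What the plan says.** The protocol article, Statistical analysis, answers the efficacy question in two sentences. The first is that "we will use a chi-square analysis comparing the observed absolute risks across treatment groups". The second begins "In addition, treatment efficacy will be assessed using a Cox regression model" and promises a hazard ratio with a 95% confidence interval. Neither analysis is called primary, both fall under the same two-sided 0.05 criterion, and the absolute risks are attached to no time point.

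Sample size considerations works with 5-year risks: "the 5-year-risk in the control group is assumed 24" per cent, and "the 5-year risk of cardiovascular morbidity and mortality will be 17.4 % in the intervention group". The total "with a two-sided alpha of 0.05 and 80% power will be 1222".

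The same section describes the monitoring: "Sequential analyses are performed on survival outcome variables according to the double triangular test". Looks take place every three months. They are justified by an expected saving in patients when the effect is real or can no longer be shown.

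The abstract, End points and follow-up, and the Conclusion all plan five years of follow-up for every participant. The Conclusion shows that entry is staggered: recruitment began in January 2005, and 228 patients had been included at the time of writing.

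**The concern.** A chi-square on crude proportions uses only whether an event has been seen, not how long the patient was observed. A patient followed for six months without an event counts the same as one followed for five years. The test that may end the trial does use time. A sequential design meant to save patients saves them only by stopping during recruitment, and at such a stop follow-up ranges from almost nothing upwards.

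Two things are at stake. First, absolute risks calculated at that moment would depend on the calendar date of the stop and could not be set against the planned 24% and 17.4%. An absolute risk reduction, or a number needed to screen derived from it, would carry the same fault. Second, two analyses at the same significance level with no stated order leave open which one decides if they disagree.

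**Working it through.** **Inputs from the article.** Control 5-year risk p0 = 0.24; imaging-arm 5-year risk p1 = 0.174; total 1222, so 611 per arm at 1:1; two-sided alpha 0.05; power 80%. (17.4% against 24% is a relative reduction of 27.5%, not the stated 24%. That is a separate matter; the two risks are used here as given.)

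**Assumptions, not in the article.** Constant hazards, uniform accrual over 4 years, and the same censoring in both arms.

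**Step 1: the plan's own figure.** For two proportions,

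n per arm = [1.960·√(2·0.207·0.793) + 0.842·√(0.24·0.76 + 0.174·0.826)]² / 0.066² ≈ 591,

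or 1182 in total. With continuity correction it is 621 per arm, 1242 in total. The stated 1222 lies between the two, and 611 per arm gives 81.3% power. The sizing therefore fits a comparison of two proportions at a fixed 5-year horizon, and a chi-square on complete 5-year data would match it.

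**Step 2: hazards.** λ = −ln(1 − p)/5 gives λ0 = 0.0549 and λ1 = 0.0382 per year, a hazard ratio of 0.697.

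**Step 3: crude risk when follow-up is spread uniformly from a to b years.**

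risk = 1 − [exp(−λa) − exp(−λb)] / [λ(b − a)].

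A stop at year 4 gives a = 0, b = 4:
- control: 1 − (1 − 0.8029)/0.2195 = 10.2%
- imaging: 1 − (1 − 0.8582)/0.1529 = 7.3%

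The unrounded difference is 2.945 points.

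| Follow-up at analysis | Control | Imaging | Difference (points) | Risk ratio |
|---|---|---|---|---|
| 5 years for all | 24.0% | 17.4% | 6.6 | 0.725 |
| 2 to 5 years | 17.4% | 12.5% | 4.9 | 0.718 |
| 1 to 5 years (stop at year 5) | 15.0% | 10.7% | 4.3 | 0.716 |
| 0 to 5 years | 12.6% | 9.0% | 3.6 | 0.715 |
| 0 to 4 years (stop at year 4) | 10.2% | 7.3% | 2.9 | 0.712 |

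**Step 4: does the test itself suffer?** Expected events d = 611 × (sum of the two crude risks). Log-rank power = Φ(|ln 0.697|·√(d/4) − 1.960). Each row is a single analysis at 0.05.

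| Follow-up | Events | Chi-square power | Log-rank power |
|---|---|---|---|
| 5 years for all | 253 | 81.3% | 82.0% |
| 2 to 5 years | 182 | 67.3% | 68.5% |
| 0 to 5 years | 132 | 52.2% | 54.5% |
| 0 to 4 years | 107 | 44.5% | 46.4% |

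Most of the power lost to short follow-up is lost by both tests. In 4000 simulated trials with no effect and follow-up of 0 to 5 years in both arms, the chi-square rejected in 4.7% and the log-rank in 4.5%.

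**The case against.** The strongest reply is that the article plans five years for everyone. Staggered entry then does no harm: apart from losses, the crude proportion is the 5-year risk, and it is the quantity that the sample size compares. This stands. A reader might infer that the reported risks are bound to differ from the 5-year risks, but the documents do not support that. The article does not say that follow-up of enrolled patients ends when a boundary is crossed, nor when the final chi-square would be run. It gives no boundary parameters or accrual rate from which a likely stopping date could be derived.

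Three other strong readings also fail.
- That the chi-square understates the benefit: this is true of the absolute difference only, since the ratio barely moves.
- That the test is invalid: with equal censoring its error rate is kept and it gives up about 2 points of power.
- That unequal loss to follow-up biases the comparison: the article gives no loss rate and no sign of imbalance. Both arms complete the same half-yearly forms, endpoint classification is blinded, and only groups B and C (8% + 22% = 30% of the imaging arm) are sent to a cardiologist. Informative loss would bias Cox and Kaplan-Meier as well.

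It is also fair that Cox is already planned, that the words introducing it do not make it subordinate, and that a condensed article leaves detail to the full protocol. But the chi-square on crude risks is a stated choice, not an omitted detail. Finally, a conventional Cox p-value after a sequential stop can itself disagree with the boundary. That needs a sequence-adjusted analysis and is a separate matter.

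**Conclusion.** The point holds conditionally. The plan names first an efficacy analysis that ignores follow-up time, ties its risks to no time point, and does not rank it against Cox, while the monitoring uses time to event. With complete five-year follow-up little is lost. With an analysis at an early stop, or with incomplete follow-up, the crude proportions are no longer 5-year risks. Under constant hazards and uniform 4-year accrual, the absolute difference is about 3 points at year 4 and 4.3 points at year 5, against 6.6 planned. The hazards and the accrual pattern are assumptions, and another pattern would move these figures. The harm is to the meaning of the absolute risks and to the clarity of which result decides, not to the validity of the test.

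**What to change.** Name time to first primary event as the primary analysis, with a log-rank or Cox score test in line with the sequential test and stratified by hospital, since randomisation is per hospital. Give the Cox hazard ratio with its 95% confidence interval as the relative measure. As the absolute measure, report Kaplan-Meier or cumulative-incidence risks at 5 years by arm and their difference with a 95% confidence interval. Cumulative incidence allows for non-vascular death, which is not part of the composite. Keep the chi-square for a descriptive table only, labelled with the follow-up it covers.

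This changes only the analysis wording. Event dates are already needed for the Cox model and the monitoring, and neither the sample size nor the data collection has to change.

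### The plan monitors the primary outcome with a double triangular test but analyses it with a fixed-sample p < 0.05 and an ordinary Cox interval, without saying which rule decides the trial

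*Protocol article*

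**What the plan says.** Sample size considerations sets the monitoring: "Sequential analyses are performed on survival outcome variables according to the double triangular test", carried out in PEST version 4. On timing: "The sequential (interim) analyses will be performed every three months by an independent data safety monitoring board (DSMB"). The stated purpose is to need fewer patients on average, whether the expected difference is real or no difference can be expected any more. The section plans 1222 patients at two-sided alpha 0.05 and 80% power, for 5-year risks of 24% and 17.4%.

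Statistical analysis sets the test and the estimate. For the test: "we will use a chi-square analysis comparing the observed absolute risks across treatment groups". For the estimate: "treatment efficacy will be assessed using a Cox regression model and expressed as a hazard ratio with corresponding 95 % confidence intervals". The threshold is "Associations will be considered significant at p < 0.05", with "All statistical tests will be 2 sided", and the software is different: "For statistical analyses we will use SPSS".

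No sentence links the two sections. The Data Safety and Monitoring Board section repeats the three-monthly schedule and does not say which rule governs the conclusion.

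**The concern.** Two decision rules are written for one outcome. Under the sequential design, the conclusion depends on which boundary the score statistic crosses. Under the analysis section, it depends on whether a conventional p-value falls below 0.05. A trial can end in a place where the two disagree, and the text does not say which one readers should take as the result.

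Estimation is also affected. A trial stopped because the observed effect is large tends to stop on a random high. A conventional Cox estimate at that moment is therefore too favourable, and its 95% interval covers less than 95%. Early stopping is a stated aim of this design, so the headline hazard ratio is exposed.

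**Working it through.** **Inputs from the article:** 5-year risks 24% and 17.4%, 1:1 allocation, two-sided alpha 0.05, 80% power, N = 1222, looks every three months, double triangular test.

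**Assumptions, because the article does not give them:** the double triangular test is built from two one-sided 0.025 triangular tests at 80% power; looks are equally spaced in information (20 or 36 of them); the correction for discrete looks is 0.583·√(increment in V).

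**1. The plan's own figure.** Comparing two proportions at 24% and 17.4% gives a total of 1182 without continuity correction and 1242 with it. Freedman's formula gives 246 events, about 1188 patients. With 611 per arm the power is 81.3%. So 1222 reproduces as a fixed-sample size, with no enlargement for sequential monitoring.

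**2. Boundaries.**
- Hazard ratio = ln(1 − 0.174)/ln(1 − 0.24) = 0.697, so θ = 0.3616.
- Corrected θ′ = 2 × 1.96/(1.96 + 0.8416) × 0.3616 = 0.506.
- a = 2·ln(20)/θ′ = 11.84; c = θ′/4 = 0.1265.
- Outer boundary: Z = a + cV. Inner (no-difference) boundary: Z = −a + 3cV. They meet at V = a/c = 93.6, about 374 events.

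**3. Where 1222 patients would leave the trial.**
- Expected events = 611 × (0.24 + 0.174) = 253, so V ≈ 253/4 = 63.2.
- Outer boundary: (11.84 + 0.1265 × 63.2)/√63.2 = 2.49. With the discrete-look correction it is about 2.36 to 2.40, two-sided p about 0.016 to 0.018.
- Inner boundary: (−11.84 + 0.3795 × 63.2)/√63.2 = 1.53 before correction.
- So the boundaries are still open. A final |z| between 1.96 and about 2.4 is significant under Statistical analysis and undecided under the sequential design.
- The uncorrected outer boundary never falls below 2√(ac) = 2.45, so disagreement arises essentially in one direction.

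**4. Type I error** (200,000 simulated score paths per setting):

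| Monitoring ends at | By boundary | By p < 0.05 on the data at stopping |
|---|---|---|
| V = 63.2 (253 events) | 4.3–4.4% | 5.9–6.0% |
| V = 73.3 (293 events = 1222 × 24%, the null expectation) | 4.9% | 5.4% |
| V = 93.6 (closure) | 5.0% | 5.3% |

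At V = 63.2 the gap between the columns (about 1.6 points) comes entirely from trials that end with no boundary reached. If the no-difference boundary is not treated as binding, the p < 0.05 rule gives about 6.6% at V = 63.2.

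**5. Estimation under the planning effect (true hazard ratio 0.70), analysis at stopping.**
- Median unadjusted hazard ratio: 0.67 over all trials, and 0.63 (V = 63.2) to 0.64 (closure) among trials stopped for benefit.
- Coverage of the nominal 95% interval: about 93%.
- About 6% of trials cut off at V = 63.2 end with |z| > 1.96 and no efficacy crossing.
- If the trials stopped for benefit were followed on to the full V = 63.2, their median hazard ratio would be 0.67.

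**The case against.** - **The design already controls alpha.** This stands. Decisions taken by the boundaries keep the error at or below about 5%. A reader might infer the large inflation that comes from testing at 0.05 every quarter (28 to 30% in simulation). The article does not propose that; the quarterly looks use the boundaries.
- **Most of the excess type I error is not caused by the repeated looks.** This also stands. It comes mainly from ending at a fixed-sample number of patients before the boundaries close. Run to closure, the p < 0.05 rule gives only about 5.3%.
- **Follow-up may continue after stopping.** The article states five years of follow-up for all participants and describes the sequential gain as fewer patients. If stopping ends only recruitment, later data dilute the bias, and a single test at the full planned information has 5.0% type I error. The article does not settle which applies, so the estimation figures are conditional on analysis at stopping.
- **The 0.63 to 0.64 is conditional on stopping for benefit.** A median-unbiased estimate corrects the unconditional bias, here 0.67 against 0.70. It is not shown to remove the whole conditional exaggeration.
- **Adjusted estimates are analysis-plan detail, and the threshold sentence is a general convention.** This is only partly right. The article does not leave the test, interval and threshold open. It fixes fixed-sample versions beside a sequential design and gives no order of precedence.

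One further inference should be avoided. The sentence "Since this is a randomized controlled trial, no adjustments will be made, although centers may be added" might be read as refusing any sequential adjustment. In context it concerns covariates and centre, and this point does not rely on it.

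**Conclusion.** The conflict is in the text as written: one primary outcome, two decision rules, no precedence. Its main cost is a hazard ratio that is too favourable and a 95% interval that covers about 93%, if the analysis is done at stopping and the planning effect is true. The type I effect is modest, from about 5.3% to about 6% depending on whether the boundaries close, or about 6.6% if the no-difference boundary is not followed. The article does not support a claim that the sequential test itself fails to control error. It also does not support one that every early stop would mislead to the full conditional extent. All sizes depend on the assumed boundary construction, number of looks and information at the end. The direction was the same under 32 to 48 looks and under boundaries built for 90% power, where the p < 0.05 rule gave about 5.9% and coverage 91 to 92%.

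**What to change.** In Statistical analysis, state that the double triangular boundary decision is the primary conclusion. Add that an underrunning analysis applies if the trial ends with no boundary reached, and an overrunning analysis if data arrive after stopping. For the primary outcome, report the sequentially adjusted p-value, the median-unbiased hazard ratio and the adjusted 95% interval from the sequential software already named. Label the ordinary chi-square p-value and Cox interval as descriptive for that outcome. Say also whether follow-up continues after a stop and which data set the primary estimate uses.

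The cost is wording, a little more analysis work and a slightly less favourable reported estimate. The Conclusion reports 228 patients included of about 1200, so at that point the change could still be made early in the trial.

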## Conclusion

Peripheral arterial disease is a common disease among elderly persons and is associated with a very high risk of cardiovascular events. In this study patients with peripheral arterial disease, but without cardiac symptoms, are randomized to an imaging arm consisting of multi-detector CT angiography of the coronary arteries and dobutamine stress MRI or to a control group in which case only a coronary calcium CT scan will be performed at baseline. In case of a positive finding in the imaging arm, patients are referred to a cardiologist who will take appropriate action. All participating patients will enter a 5-year follow-up for the occurrence of cardiovascular events. To the best of our knowledge GROUND is the first large trial designed to assess the value of multi-detector CT and MRI stress testing in reducing the morbidity and mortality of patients with peripheral arterial disease but yet without cardiac symptoms. At the time of writing this manuscript all centers are actively enrolling patients. The first patient enrolled in January 2005. The number of included patients is currently 228.

### Data Safety and Monitoring Board

The data safety and monitoring board performs statistical analyses of un-blinded interim data and formulates recommendations for the Steering Committee on the continuation of the trial. The DSMB may also offer unsolicited recommendations on the continuation of the trial, for example after publication of results of similar trials. Every three months the chair of the DSMB will be provided an interim dataset to perform sequential analyses. When appropriate, given the results from the interim analysis, the chair will call for a meeting with the other DSMB members. Members of the Data Safety and Monitoring Board are: [name], PhD (statistician); [name], PhD (cardiologist); [name], MD, PhD (epidemiologist); [name], PhD (epidemiologist).
